### **2) Hypothesis and Objectives**

The present study is conducted to compare the 1-year morphologic features of NT-SV used as Y-composite grafts based on the in situ LITA with those of NT-SV used as aorto-coronary

grafts.

We hypothesize that the intima-media thickness (IMT) of the SV from aortocoronary configuration is higher than that of the SV from Y-composite configuration at 1-year angiographic follow-up and IVUS study.

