### **Intravascular ultrasonographic (IVUS) study**

The IVUS study will be performed after the completion of 1-year postoperative angiography in a standard fashion using an automated motorized pullback system (0.5 mm/s) with commercially available imaging catheters (Boston Scientific/SCIMED, Minneapolis, Minnesota, USA). The IVUS images will be acquired after the administration of 100 to 200 mg of nitroglycerin. In case of Y-composite grafting, the IVUS catheter will be advanced into the SV conduit connected to the mid-portion of the LITA and located at around 5 cm distal to the Y-anastomosis, and a pullback will be performed for the total length of 10 cm. To avoid the influence of suture materials, the areas 1 cm proximal and distal from the Y-anastomosis will be excluded from the analysis. In case of aortocoronary grafting, the IVUS catheter will be advanced into the SV conduit and located at around 5 cm distal to the aortocoronary anastomosis, and a pullback will be performed for the total length of 5 cm. The IVUS catheter will be also advanced into the LITA conduit and located at around 15 cm distal to the subclavian arterial origin, and an automated motorized pullback will be performed for the total length of 10 cm. To be a reference to the Y-composite group, the areas 1 cm distal from the aortocoronary anastomosis and the middle 2cm of evaluated LITA will be excluded from the analysis. The IVUS analysis will be performed by 1 independent experienced observer. Quantitative analyses of the IVUS data will be performed using computerized planimetry software (echoPlaque 3.0, Indec Systems Inc, Santa Clara, California, USA).

The lumen and vessel areas will be measured every 1 millimeter. All volumes will be calculated using the Simpson rule and then normalized for analyzed length. The area of intima-media (IM) will be calculated by subtracting the luminal area from the vessel area. The proportion of IM area to vessel area will be also calculated.

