## **2) Outcome measures**

- 1) Demographics: age, sex, height, weight, body mass index, body surface area, diagnosis,

operation name

2) Preoperative data

- Risk factors: diabetes mellitus, hypertension, smoking, dyslipidemia, stroke, chronic obstructive pulmonary disease, chronic kidney disease, chronic liver disease, coronary disease, peripheral vascular disease, history of cardiac surgery, New York Heart Association functional class, STS mortality risk, EuroSCORE II, SYNTAX score
- Electrocardiography
- Pulmonary function test
- Laboratory tests
- Echocardiographic measurements: LV ejection fraction, LV end diastolic dimension, LV end systolic dimension, regional wall motion abnormalities, etc.
- Coronary angiography : 1-vessel disease/2-vessel disease/3-vessel disease/left main disease, degree of stenosis for each branch

3) Operative data: number of anastomoses, target vessels, location of anastomosis, operative findings

4) Postoperative data

- Early clinical outcomes: op mortality, op morbidities (low cardiac output, bleeding reoperation, perioperative myocardial infarction, perioperative stroke, acute kidney injury, respiratory complications, postoperative atrial fibrillation, and mediastinitis)
- Echocardiographic measurements: LV ejection fraction, LV end diastolic dimension, LV end systolic dimension, regional wall motion abnormalities, etc.
- Coronary angiography : patency of bypass grafts, patency of distal anastomoses, presence of competitive flows for each anastomosis

5) 1-year follow-up data

- Clinical outcomes: all-cause mortality, cardiac mortality, major adverse cardiac events, reintervention, target vessel revascularization
- Echocardiographic measurements: LV ejection fraction, LV end diastolic dimension, LV end systolic dimension, regional wall motion abnormalities, etc.
- Coronary angiography : patency of bypass grafts, patency of distal anastomoses, presence of competitive flows for each anastomosis
- Intravascular ultrasound (IVUS) : intima-media thickness (IMT), lumen diameter (LD)

※ Primary clinical endpoint

Intima-media thickness (IMT) measured by IVUS on 1-year angiogram

※ Secondary clinical endpoint

Luminal diameter measured by IVUS on 1-year angiogram

One-year angiographic graft patency

Clinical outcomes including all-cause mortality, cardiac death, target vessel revascularization, and reintervention at 1 year

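### The protocol states no masking of the single IVUS reader of the primary endpoint, although the acquisition it describes reveals the arm

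*Protocol*

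**What the plan says.** Section 10, Outcome measures, names the primary endpoint: "Intima-media thickness (IMT) measured by IVUS on 1-year angiogram". The IVUS section assigns all of the reading to one person: "The IVUS analysis will be performed by 1 independent experienced observer". Lumen and vessel areas are traced at 1 mm steps with planimetry software, and the wall area is the difference between the two.

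The same section sets a different acquisition for each arm:

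- **Composite group:** the catheter is "located at around 5 cm distal to the Y-anastomosis, and a pullback will be performed for the total length of 10 cm".
- **Aorta group:** the catheter is "located at around 5 cm distal to the aortocoronary anastomosis, and a pullback will be performed for the total length of 5 cm". A second run follows: "The IVUS catheter will be also advanced into the LITA conduit", with a 10 cm pullback.

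The exclusion zones also differ. In the Composite group, "the areas 1 cm proximal and distal from the Y-anastomosis will be excluded from the analysis". In the Aorta group, "the areas 1 cm distal from the aortocoronary anastomosis and the middle 2cm of evaluated LITA will be excluded from the analysis".

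Section 8, Hypothesis and Objectives, states the expected direction: "We hypothesize that the intima-media thickness (IMT) of the SV from aortocoronary configuration is higher than that of the SV from Y-composite configuration".

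The protocol as shown says nothing about blinding this observer, coding or cropping the recordings, or the order in which they are read.

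**The concern.** The surgeons cannot be blinded to graft configuration, so the reading of the images is where blinding can be achieved. The protocol describes the reader's standing (independent, experienced) but not what the reader is allowed to see. It also describes recordings whose length, number and content differ by arm.

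Border tracing involves judgement. Because wall area is vessel area minus lumen area, a small habitual difference in where either border is drawn passes straight into the endpoint. If that difference goes with the arm, it is a systematic error. Measuring more frames or enrolling more patients does not average it out, and the intention-to-treat and per-protocol t-tests would both use the same readings. The declared direction gives a knowing reader an expectation to meet, even without intent.

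**Working it through.** **1. Does the described acquisition reveal the arm?**

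| Feature | Composite | Aorta |
|---|---|---|
| Vein recording | one 10 cm run | one 5 cm run |
| Content | about 5 cm vein, the Y-anastomosis, about 5 cm LITA | about 5 cm vein, ending at the aortic anastomosis |
| LITA recording | part of the same run | separate 10 cm run |
| Excluded | 1 cm either side of the Y | 1 cm beyond the aortic anastomosis; middle 2 cm of the LITA run |

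Run length, number of runs and the continuous passage from vein through the Y into the LITA each identify the arm. Whoever applies the exclusion zones must also find a landmark specific to the arm, and the section names nobody for this except the one observer.

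**2. Are the identifying frames needed for the primary reading?** In both arms the vein is imaged from about 5 cm back to the proximal anastomosis, and the nearest 1 cm is dropped: 5 − 1 = 4 cm, at nominally 1 to 5 cm from the anastomosis. The analysed vein segment is therefore the same in both arms and contains no anastomosis.

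**3. The plan's own sample size** (section 9, Sample size calculation: SDs 0.12 and 0.09 mm, means 0.31 and 0.43 mm, two-sided α 0.05, power 90%, dropout 30%).

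- n = (1.960 + 1.282)² × (0.12² + 0.09²) / 0.12² = 10.51 × 0.0225 / 0.0144 = 16.42, rounded up to 17 per group.
- 17 / 0.70 = 24.3, rounded up to 25 per group, 50 in total.

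Both stated figures reproduce, and this point disputes neither.

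**4. Sensitivity of the primary test to an arm-linked reading shift.** Set the true difference to 0 and add a constant shift b to the measured IMT of one arm.

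- SE = √((0.12² + 0.09²) / n): 0.0364 mm at 17 per arm, 0.0300 mm at 25 per arm.
- Smallest observed difference with p < 0.05 is t(0.975; 2n − 2) × SE: about 0.074 mm at 17 per arm, 0.060 mm at 25 per arm.
- The rejection rate comes from the noncentral t distribution with 2n − 2 degrees of freedom and noncentrality b / SE. For b = 0.02 mm and n = 17, the noncentrality is 0.02 / 0.0364 = 0.55.

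| Assumed shift b (mm) | Share of planned 0.12 mm | Two-sided rejection, 17 per arm | 25 per arm |
|---|---|---|---|
| 0 | 0 | 5.0% | 5.0% |
| 0.01 | 1/12 | 5.8% | 6.2% |
| 0.02 | 1/6 | 8.3% | 10.0% |
| 0.03 | 1/4 | 12.6% | 16.5% |
| 0.05 | 5/12 | 26.6% | 37.2% |

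The rate rises with sample size because the shift stays fixed while the standard error shrinks. The shifts are assumptions, since the documents give no reader error or reproducibility figure.

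**The case against.** The strongest objection is that the protocol describes acquisition, not hand-over. A reader might infer that the endpoint is read unblinded. The text does not say so, and an imaging manual that is not shown could include cropping and coding. That part stands: what the document supports is that no masking is stated and that the recordings as acquired would give the arm away. It does not dispose of the point. The section already fixes who reads, with which tool and which segments, and masking of that reader belongs in the same place. It is a matter of trial conduct, not an analysis detail normally left to a statistical analysis plan.

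It is also tempting to say that seeing the LITA identifies the arm. It does not: the LITA is imaged in both groups, and the Aorta exclusions were chosen so that its segments serve as a reference for the Composite group. The cue is the continuous run through the Y, together with run length and number.

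The safeguards in the plan count for something. Motorised pullback, a fixed 1 mm sampling step and planimetry software limit the choice of frames, and an independent reader reduces conflict of interest. The test is two-sided, and nothing shows that the reader knows or favours the hypothesis. None of this hides the arm.

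The rates in the table are not estimates of this trial's error rate. At 0.01 mm the effect is slight. The plan also requires both the intention-to-treat and the per-protocol analysis to be significant, so at a given number analysed the single-test rates are upper limits for the trial's conclusion. The reduction is small if the two sets largely coincide.

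**Conclusion.** The point holds in this form: the protocol states no masking for the only reader of its primary endpoint, while the acquisition it prescribes reveals the arm. Calling the observer independent does not fill that gap. The document does not establish that the reading is unblinded in practice, and it gives no evidence of actual bias.

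The size is conditional. Assumed arm-linked shifts of 0.01 to 0.05 mm take the false-positive rate from 5% to between 5.8% and 26.6% at 17 per arm, and to between 6.2% and 37.2% at 25 per arm. These rates rest on the plan's SDs, a constant shift, no true difference and a single t-test. The sample size of 17 evaluable per group and 50 in total is unaffected. This is an avoidable weakness in the primary endpoint that should be corrected. It is not an error in a stated figure.

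**What to change.** Have an existing team member other than the reader prepare the recordings before any reading:

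1. Apply the exclusion zones and crop each vein recording to the common analysed segment, nominally 1 to 5 cm distal to the proximal anastomosis.
2. Remove identifiers and all anastomosis frames, and code the clips.
3. Give the clips to the same observer in random order, without the angiogram or the allocation.
4. Lock the vein lumen and vessel areas before any LITA run is opened.

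Amend the observer sentence in the IVUS section to say that the observer is blinded to allocation and reads coded saphenous vein segments. The segment length should be given as nominal, because the catheter position is itself only approximate.

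The cost is cropping and coding about 35 vein recordings if the full 30% dropout occurs (50 × 0.70), or up to 50 if nobody drops out, and withholding the LITA runs meanwhile. The person who crops must be able to find the anastomosis on IVUS. Masking may remain imperfect if the appearance of the graft itself hints at the arm; the protocol's background already reports negative remodelling of composite vein grafts. No extra patient procedure is needed.

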## **2) Outcome measures**

- 1) Demographics: age, sex, height, weight, body mass index, body surface area, diagnosis,

operation name

2) Preoperative data

- Risk factors: diabetes mellitus, hypertension, smoking, dyslipidemia, stroke, chronic obstructive pulmonary disease, chronic kidney disease, chronic liver disease, coronary disease, peripheral vascular disease, history of cardiac surgery, New York Heart Association functional class, STS mortality risk, EuroSCORE II, SYNTAX score
- Electrocardiography
- Pulmonary function test
- Laboratory tests
- Echocardiographic measurements: LV ejection fraction, LV end diastolic dimension, LV end systolic dimension, regional wall motion abnormalities, etc.
- Coronary angiography : 1-vessel disease/2-vessel disease/3-vessel disease/left main disease, degree of stenosis for each branch

3) Operative data: number of anastomoses, target vessels, location of anastomosis, operative findings

4) Postoperative data

- Early clinical outcomes: op mortality, op morbidities (low cardiac output, bleeding reoperation, perioperative myocardial infarction, perioperative stroke, acute kidney injury, respiratory complications, postoperative atrial fibrillation, and mediastinitis)
- Echocardiographic measurements: LV ejection fraction, LV end diastolic dimension, LV end systolic dimension, regional wall motion abnormalities, etc.
- Coronary angiography : patency of bypass grafts, patency of distal anastomoses, presence of competitive flows for each anastomosis

5) 1-year follow-up data

- Clinical outcomes: all-cause mortality, cardiac mortality, major adverse cardiac events, reintervention, target vessel revascularization
- Echocardiographic measurements: LV ejection fraction, LV end diastolic dimension, LV end systolic dimension, regional wall motion abnormalities, etc.
- Coronary angiography : patency of bypass grafts, patency of distal anastomoses, presence of competitive flows for each anastomosis
- Intravascular ultrasound (IVUS) : intima-media thickness (IMT), lumen diameter (LD)

※ Primary clinical endpoint

Intima-media thickness (IMT) measured by IVUS on 1-year angiogram

※ Secondary clinical endpoint

Luminal diameter measured by IVUS on 1-year angiogram

One-year angiographic graft patency

Clinical outcomes including all-cause mortality, cardiac death, target vessel revascularization, and reintervention at 1 year

### **3) Differences from previous treatments and studies**

Both of the configurations, Y-composite and aortocoronary, are commonly used in clinical practice, and have demonstrated good long-term outcomes in many previous studies.

When compared with previous studies, the present study is the first prospective randomized controlled trial comparing the morphologic change of SV graft using IVUS measurements.

### **4) Risks associated with the study**

#### **\* Predicted risks**

Because both configurations have proved their efficacy and safety by prospective and many retrospective studies, the predicted risks associated with the present study will be comparable to routinely performed CABG.

If any adverse event or risk occurs, providing the standard management for them will be sufficient.

### **5) Criteria for suspension and dropout**

Patients who decline to participate in the trial are suspended or drop-out

### **6) Safety**

Safety outcomes will be a composite of death from any cause and individual major postoperative complications including low cardiac output, bleeding reoperation, perioperative myocardial infarction, perioperative stroke, acute kidney injury, respiratory complications, postoperative atrial fibrillation, and mediastinitis.

All safety outcome measures will be assessed and recorded at designated time intervals by research personnel at the center. Data regarding every event will be reviewed and adjudicated by the principal investigator and sub-investigator.

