#### Operative strategies and Randomization process

Surgeries will be performed under standard median sternotomy, and off-pump CABG (OPCAB) will be the preferred grafting strategy during the study period. The in situ LITA will be

harvested using the skeletonization technique. The SV will be simultaneously harvested, preferentially from the lower leg, using a NT technique that retains perivascular soft tissue as previously described. Randomization will be performed after the conduits are harvested without injury and it is confirmed that the intraoperative findings indicate that either of the grafting strategies are feasible. Web-based block randomization will be performed using randomly determined block sizes of 4 and 6. After randomization, the procedures will be performed according to the assigned grafting strategy. In the patients assigned to the Composite group, the Y-composite graft is constructed first by anastomosis of the distal end of the SV graft to the side of the LITA, and anastomosis of the LITA to the LAD territory is performed whenever necessary. The SV is then anastomosed to the diagonal branch, to the vessels in the left circumflex coronary artery(LCX) territory, and then to the vessels in the right coronary artery(RCA) territory as needed using a sequential anastomotic technique. In the patients assigned to the Aorta group, the SV is first anastomosed to the ascending aorta using the Heartstring III Proximal Seal System (MAQUET Holding B.V. & Co. KG, Rastatt, Germany). The LITA is then anastomosed to the target vessel in the LAD territory. Finally, the SV is anastomosed sequentially to the diagonal branch, to the vessels in the LCX territory and then to the vessels in the RCA territory as needed using a sequential anastomotic technique.

※ Randomization : Patients who meet the inclusion criteria and the exclusion criteria are randomly assigned to 1 of the 2 configurations in a 1:1 manner. Randomization is performed with a web-based block randomization method (<https://mrcc.snuh.org/>) with randomly determined block sizes of 4 and 6.

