### **7) Efficacy**

Efficacy analysis will be performed for ITT (*Intention to treat*) group, and supplemental

analysis will be performed for PP (*Per protocol*) and *As treated* group. The primary endpoint will be concluded as 'significantly different' if both ITT and PP analyses confirm the significance of difference.

ITT group includes all study population. PP group is constituted from the ITT group after excluding the patients with major violation of the study protocol.

The null hypothesis is that the IMT of Y-composite group is comparable to that of aortocoronary group measured by IVUS on 1-year angiogram. The result for the primary endpoint will be presented with 95% two-sided confidence interval for mean difference between groups. The superiority test will be performed using a t-test which compared mean difference between groups under the two-sided significance level of 0.05.

For analysis of 1-year clinical outcomes, including all-cause mortality, cardiac death, target vessel revascularization, and reintervention, events will be counted at postoperative 1 year, and comparisons between the 2 groups will be made using the chi-square test and Fisher's exact test. A P value of  $< .050$  will be considered statistically significant.

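### Investigators adjudicate every event and no masking to graft configuration is described, which leaves the judgement-based safety and secondary outcomes open to detection bias (minor)

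*Protocol*

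**What the plan says.** Section 10, 6) Safety, divides the work in two. Collection falls to local staff: "All safety outcome measures will be assessed and recorded at designated time intervals by research personnel at the center". Classification falls to the trial's leaders: "Data regarding every event will be reviewed and adjudicated by the principal investigator and sub-investigator". The outcomes in that section are introduced as follows: "Safety outcomes will be a composite of death from any cause and individual major postoperative complications including low cardiac output, bleeding reoperation, perioperative myocardial infarction", and the list continues with further complications.

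Under 2) Outcome measures, the last secondary endpoint reads: "Clinical outcomes including all-cause mortality, cardiac death, target vessel revascularization, and reintervention at 1 year". Section 7) Efficacy says how these are compared: "events will be counted at postoperative 1 year, and comparisons between the 2 groups will be made using the chi-square test and Fisher's exact test", with significance at P below .050.

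Two other statements bear on the point. Under Operative strategies and Randomization process, assignment follows conduit harvest, and then: "After randomization, the procedures will be performed according to the assigned grafting strategy". For the imaging endpoint, the IVUS section says: "The IVUS analysis will be performed by 1 independent experienced observer".

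**The concern.** Who adjudicates is a design decision, and this protocol makes it: the investigators running the trial classify the events. The text available has no step that keeps the graft configuration from them. The operating team necessarily knows the arm, and operative records and later angiograms would normally show it.

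Some outcomes leave room for judgement. A death has to be called cardiac or not, and a repeat procedure has to be attributed to a target vessel or to something else. Low cardiac output, perioperative myocardial infarction and respiratory complications each depend on a threshold or an interpretation. If borderline cases are read even slightly differently by arm, the recorded rates differ for a reason unrelated to the grafts. In a trial this small, a few such readings are a visible share of the events. At stake are the safety comparison and the clinical part of the secondary endpoints.

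**Working it through.** **Step 1: the number per arm.** Inputs are from section 9, 3) Sample size calculation: means 0.31 and 0.43 mm, SDs 0.12 and 0.09 mm, two-sided α 0.05, power 90%, dropout 30%. With the protocol's own formula:

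n = (1.960 + 1.282)² × (0.12² + 0.09²) / 0.12² = 16.42, rounded up to 17 per group.

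17 / 0.70 = 24.3, rounded up to 25 per group and 50 in total.

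The stated figures reproduce. They rest on IMT alone, so no change to adjudication alters them.

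**Step 2: which outcomes depend on judgement.**

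| Outcome | Judgement needed | Covered by the adjudication sentence |
|---|---|---|
| IMT by IVUS | Separate independent reader | No |
| All-cause death | None | Unaffected in practice |
| Bleeding reoperation, as an occurrence | Little | Yes |
| Low cardiac output, perioperative infarction, respiratory complications | Yes | Yes |
| Cardiac death, attribution of target vessel revascularization | Yes | Only if *every event* extends to the 1-year outcomes |

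**Step 3: leverage of one classification.** 1/25 = 4 percentage points in an arm's rate.

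**Step 4: illustration with Fisher's exact test, 25 per arm, two-sided.** The protocol gives no event rates, so these counts are assumed:

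- 5 v 0: P = 0.0502; 6 v 0: P = 0.0223
- 6 v 1: P = 0.0983; 7 v 1: P = 0.0488

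One classification can cross .050, but only at counts of 5 to 7 in one arm (20% to 28%) against 0 or 1 in the other.

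**Step 5: illustration over all possible counts.** Assume equal true rates in both arms, and over-calling in one arm only. The chance that Fisher's test gives P below 0.05 is:

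| Assumed true rate | No over-calling | +5 points (1.25 patients) | +10 points (2.5 patients) |
|---|---|---|---|
| 10% | 0.9% | 2.9% | 8.6% |
| 20% | 2.2% | 3.4% | 6.9% |
| 30% | 2.3% | 3.4% | 7.0% |

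Fisher's test is conservative at this size. Over-calling by 5 points raises the false-positive rate but leaves it below the nominal 5%. Over-calling by 10 points, all in one arm, takes it above.

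**The case against.** The case for leaving the text alone is substantial. Four stronger readings are tempting, and the protocol does not support them.

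- **That the trial is declared open-label, or that adjudication is declared unmasked.** Neither is stated. The Safety section says who adjudicates, not what they are shown. Some sections are absent from the public text, so the accurate statement is that no masking is described in what is available. What stands without inference is that the adjudicators are the trial's own investigators and that the operating team knows the arm.
- **That every 1-year endpoint is certainly adjudicated this way.** The sentence sits under Safety, and the Efficacy section names no adjudicator. The extension rests on *every event*. It is a reasonable reading, but a reading.
- **That the hypothesis gives the investigators a declared direction for clinical events.** The hypothesis concerns IMT only. The section on risks treats both configurations as established and expects risks like those of routine surgery.
- **That one judgement is likely to decide significance.** The counts in step 4 have no support in the protocol. Moreover, the Efficacy section assigns its tests to the 1-year clinical outcomes and specifies none for the perioperative complications.

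It is also true that the main conclusion rests on IVUS, read by an independent observer, and that the clinical outcomes are secondary in a 50-patient morphology trial. Masking would be incomplete, because investigators may recognise their patients. Nor can masked classification correct a bias in the decision to reintervene. All of this limits the size of the point. It does not remove it: the stated procedure leaves judgement calls with investigators from whom the allocation is not shown to be withheld, and a partial safeguard is cheap.

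**Conclusion.** The point holds as a minor one, limited to secondary and safety outcomes. The exposed outcomes are low cardiac output, perioperative myocardial infarction and respiratory complications, plus cardiac death and attribution of target vessel revascularization if the adjudication sentence covers the 1-year outcomes. The only size that follows from the protocol alone is 4 percentage points per reclassified event at 25 per arm. The P values and false-positive rates above rest on assumed event rates and assumed over-calling in one direction, and show sensitivity rather than an expected effect.

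The conclusion assumes that no section missing from the public text masks the adjudicators. If one does, only the question of scope remains.

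**What to change.** Amend section 10, 6) Safety, and add one linking sentence to 7) Efficacy:

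1. The research personnel who already record outcomes prepare a summary of each event, with the allocation and graft description removed where feasible.
2. If one of the two adjudicators did not treat the patient, that person classifies first.
3. The classification is recorded before the allocation is revealed.
4. The same procedure covers the 1-year clinical outcomes.
5. Any outcome whose source unavoidably shows the configuration, such as revascularization of a graft, is reported as assessed unmasked.

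This needs no new assessor, patient or procedure, and leaves the sample size unchanged. The cost is a few sentences, some preparation of summaries and slightly slower adjudication. Masking will be incomplete in a 50-patient trial, and the report should say so.
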